Other study procedures for participants enrolled in phase 1 include:Baseline and endline survey (*n* = 640): Trained study staff will administer a structured baseline survey via phone to collect participant demographic, socioeconomic, and clinical information. The endline survey will be conducted either over the phone or at the health facility by trained study staff no earlier than 6 months post enrollment and only once linkage status has been confirmed.Medical record data abstraction: For participants who re-engage in care, study staff will retrospectively abstract data into study databases, including appointment attendance, HIV viral load, pharmacy dispensing, and current follow-up status.Viral load quantification: Viral load quantification will be conducted at intervals consistent with World Health Organization (WHO) and Tanzanian guidelines for monitoring HIV infection after re-engagement with care (SOC in all facilities). For those whose standard viral load draw schedule does not include a measurement at 6 months following study enrollment, a research viral load will be drawn. All collection, processing and analysis of blood samples will be conducted by local Tanzanian trained health workers and lab technicians. Specimens will be drawn by health facility personnel and transported to the hospital laboratory and/or regional hub, checked for quality, assigned barcodes, entered into the laboratory database, and centrifuged to retrieve plasma. Plasma will be stored and transported biweekly to testing laboratories, and results of testing will be made available within 2 days of sample arrival at the laboratory.Primary outcome measurement: We will assess the primary outcome of viral suppression 6 months after study enrollment. Those not on ART or with virologic failure (≥ 1000 copies/ml), or those who have died will be classified as not having the primary outcome. If there is no evidence of a documented HIV care visit in the participant’s medical record at any facility by 6 months after study enrollment, we will follow tracing procedures to confirm whether the individual is out of care, and if so, he/she will be classified as not in care, and not virally suppressed.

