**Fig. 3 Fig3:**
[figure not shown]
Phase 2 study flow diagram

Other study procedures for participants enrolled in phase 2 of RKPK are as follows:Baseline, midline and endline surveys: Trained study staff will administer a baseline survey on the same day as enrollment, typically at the health facility. Approximately 6 and 12 months following enrollment, trained study staff will administer a structured midline and endline questionnaire, either over the phone or at the health facility.Viral load quantification: Viral load quantification will be conducted per SOC procedures by health facility staff and at intervals consistent with WHO and Tanzanian guidelines for monitoring HIV infection. All collection, processing, and analysis of blood samples will follow the same process as the samples collected in Phase 1. For those whose standard viral load draw schedule does not include a draw at 12 months following study enrollment, a research viral load will be drawn. Six-month viral load (study secondary outcome) data collection will follow a similar procedure.Enhanced tracing: At endline only, study staff will use enhanced routine tracing procedures according to national guidelines with additional robust tracing using the same “gold-standard” tracing methods (≥ 3 tracing attempts using multiple methods) to investigate all potentially LTFU clients, confirm “silent transfers” (those who transfer to new facilities without notification of the prior facility) and deaths, and refer clients to health facilities where missing plasma specimens can be collected for viral load quantification.Primary outcome measurement: Viral suppression will be assessed 12 months after enrollment. Those not on ART or with virologic failure or those who have died will be classified as not having the primary outcome. Among those with no evidence of an HIV care visit to any facility by 12 months after study enrollment, we will follow tracing procedures to confirm if they are out of care, and if so, he/she will be classified as not in care, and not virally suppressed.

#### Phase 3

Phase 3 will commence after the conclusion of phases 1 and 2 and will include IDIs with PLHIV who participated in phase 1 or 2, clinical staff at phase 1 and 2 health facilities, HBC providers at phase 1 health facilities, and government stakeholders such as Regional or District AIDS Control Coordinators and RMOs. We will also conduct surveys with health facility staff and HBCs at phase 1 and 2 health facilities.

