### Statistical analysis

All primary and secondary outcomes are pre-registered and included in the trial statistical analysis plan (ClinicalTrials.gov; Open Science Framework). For phase 1, our primary, intent-to-treat (ITT) analysis of 6-month viral suppression will be a cluster-based permutation test on the individual-level outcome data, which accounts for clustering within the health facility. Multiple imputation will be used for all missing viral load data for those who re-linked to care but do not have a viral load quantified in our pre-specified assessment window. We will also construct a regression model to derive an RD with a 95% CI. For phase 2, the primary ITT analysis of 12-month viral suppression will be examined by study group using a generalized estimating equation that accounts for clustering within facility and adjusted for health facility, and will be expressed as a RD and 95% CI. For both phase 1 and 2 primary analyses, multiple imputation will be used for outcomes with > 5% missing and for covariates if 5% or more records have missing covariates and would therefore be excluded from adjusted analyses.

We will follow similar procedures as our primary outcome analysis described above for all secondary outcome proportions (Table 2: Secondary outcomes). For both phases 1 and 2, secondary analyses include assessing primary outcome data in complete case analyses that do not impute for missing outcome or covariate data. We will assess for heterogeneity in primary and secondary outcomes by facility characteristics, such as geographic region and facility size, and client characteristics, including sex, age, viral suppression at enrollment, and time out of HIV care (phase 1 only). Additionally, we will employ causal inference methods to estimate per-protocol estimands for phase 1 and 2 primary outcomes. Other trial outcomes include data from participant surveys and include assessments of food security, physical, sexual, and mental health, violence, participation in the labor force, household characteristics, and cash incentive usage (Table 2: Survey outcomes).

**Table 2 Tab2:** Trial secondary outcomes and survey outcomes

Outcome	Phase 1	Phase 2
*Secondary outcomes*		
Proportion with HIV viral suppression 12 months after enrollment	X	
Proportion with durable HIV viral suppression 12 months after enrollment	X	X
Appointment attendance	X	X
Cumulative incidence of mortality at 12 months after enrollment	X	X

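### The Phase 1 complete-case analysis drops re-linked participants without a viral load but keeps confirmed out-of-care participants as failures, so it is a poor check on the imputed primary result (minor)

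*Protocol article*

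**What the plan says.** The Statistical analysis section lists, among the secondary analyses of the primary outcome in both phases, "complete case analyses that do not impute for missing outcome or covariate data". For the Phase 1 primary analysis it plans multiple imputation of missing viral loads "for those who re-linked to care but do not have a viral load quantified in our pre-specified assessment window". It adds, for both phases, that "multiple imputation will be used for outcomes with > 5% missing".

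The outcome rules are in Assessments and data collection. In Phase 1, participants off ART, with virologic failure, "or those who have died will be classified as not having the primary outcome". A Phase 1 participant without a documented care visit by 6 months is scored as not in care, hence not suppressed, once tracing has confirmed that status. Phase 2 uses the same construction at 12 months: "we will follow tracing procedures to confirm if they are out of care, and if so, he/she will be classified as not in care". In both phases a research viral load is drawn where the routine schedule provides none at the endpoint.

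Power and sample size gives the Phase 1 planning rates: 72% return to care in the comparison arm, 92% suppression on ART, and so 66% suppressed, against 77% with the intervention.

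**The concern.** Whether a Phase 1 outcome can be missing depends on whether the participant returned to care, and return to care is part of the outcome. A confirmed non-returner has an outcome (failure) without any blood draw. A returner has one only if a viral load is measured. Complete-case analysis therefore removes people of whom about 92% are expected to be suppressed and leaves the confirmed failures in the denominator. Missingness completely at random among returners does not rescue it, because it is still not random across the cohort.

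What is at stake is how the result will be read. The main doubt about the imputed analysis is whether returners without a viral load are less often suppressed than those measured. Complete-case analysis does not vary that assumption. Agreement between the two could be taken as support for the primary result when that doubt has not been tested.

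**Working it through.** **Inputs.** From Power and sample size: return 0.72 (comparison arm), suppression among those on ART s = 0.92, suppression 0.66 against 0.77, ICC 0.01, 20 participants per facility, 320 per arm. Not given in the document, so assumed: the share m of returners without a viral load, and the share u of non-returners whose status is unresolved and who are also dropped.

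**The plan's own figures.** 0.72 × 0.92 = 0.662, the stated 66%. Two proportions of 0.66 and 0.77 at two-sided 5% (assumed, as Phase 1 does not state it) and 80% power need 264 per arm. The design effect is 1 + 19 × 0.01 = 1.19, and 264 × 1.19 = 314.2, so 315, against 320 stated. The sample size is consistent and is not in question.

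**Model.** To match 66% and 77% with s = 0.92, return is r = 0.66/0.92 = 0.717 and 0.77/0.92 = 0.837.

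- Full cohort: r·s.
- Complete case: r(1−m)s / [r(1−m) + (1−r)(1−u)].
- Missing counted as not suppressed: r(1−m)s.

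**Equal missingness, u = 0, viral loads missing at random among returners.** At m = 10%, comparison: 0.717 × 0.9 × 0.92 / (1 − 0.0717) = 0.594/0.928 = 0.640. Intervention: 0.837 × 0.9 × 0.92 / (1 − 0.0837) = 0.693/0.916 = 0.756.

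| m | Comparison % | Intervention % | RD, complete case | RD, missing as not suppressed |
|---|---|---|---|---|
| 0 | 66.0 | 77.0 | 11.0 | 11.0 |
| 5% | 65.0 | 76.3 | 11.3 | 10.45 |
| 10% | 64.0 | 75.6 | 11.6 | 9.9 |
| 20% | 61.6 | 74.0 | 12.3 | 8.8 |

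**Other scenarios for the complete-case risk difference (RD).**

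- No effect (r = 0.717 in both arms), equal m: bias exactly 0.
- No effect, 10% missing in comparison and 5% in intervention: +1.0 point. Reversed: −1.0.
- Planned effect, 15% in comparison and 5% in intervention: 13.5. Reversed: 9.8.
- Planned effect, 10% in comparison: the inflation disappears once intervention missingness reaches about 14%.
- Non-returners also dropped, m = 10%: u = 10% gives 11.0 (no bias) and u = 20% gives 10.3.
- Effect acting only on suppression among returners (0.85 to 0.92 at r = 0.72), m = 10%: 5.0 becomes 4.9.

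**The risk that the check should probe.** Suppose m = 10%, measured returners are 92% suppressed and unmeasured ones 60%. True suppression among returners is 0.9 × 0.92 + 0.1 × 0.60 = 0.888. The true arms are 0.717 × 0.888 = 63.7% and 0.837 × 0.888 = 74.3%, RD 10.6. Imputation from measured returners gives 66.0 and 77.0, RD 11.0. Complete case gives 64.0 and 75.6, RD 11.6. Here the complete-case RD lies beyond the imputed one, on the side away from the truth.

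**Phase 2, if all those lost are resolved as failures and s = 0.92 is borrowed from Phase 1.** With 0.70 against 0.80, the RD becomes 10.3, 10.7 and 11.4 at m = 5, 10 and 20%, instead of 10.0.

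**The case against.** Several objections stand in whole or part.

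- **A reader might infer that only returners are dropped and every non-returner is kept.** The text does not fix this. Out-of-care coding follows only once tracing has confirmed it, so unresolved non-returners may also be missing. The complete-case analysis excludes records with missing covariates too, and the Phase 1 baseline survey is by phone. Against this, the Phase 1 endline survey waits for linkage status to be confirmed, and the sample size treats attrition as part of the outcome, so few unresolved cases seem intended.
- **A reader might infer that the analysis exaggerates the effect.** That holds at the planning rates with equal missingness, but not in general, as the scenarios show. Equal missingness does not create an effect where there is none.
- **The shift is small.** The standard error of the RD at planning values is √[1.19 × (0.66 × 0.34 + 0.77 × 0.23)/320] = 3.9 points, so 0.3 to 1.3 points is roughly 0.1 to 0.3 of a standard error. The research viral load should also keep m low.
- **A reader might infer that this is the plan's only missing-data check.** The article's list of secondary analyses is not presented as exhaustive, and the SAP is not shown.
- **A reader might infer from the 5% trigger that the primary analysis could itself go unimputed.** At m = 5%, only 3.6% to 4.2% of an arm is missing (0.05 × 0.717 and 0.05 × 0.837). But the Phase 1 sentence promises imputation of all missing viral loads among the re-linked, so the article does not support that conclusion.
- **Counting missing as failure is also biased under random missingness,** by 0.55, 1.1 and 2.2 points in the table. This is correct. It can serve only as a bound.
- **Phase 2 differs.** Participants are in care at entry, the re-linked wording belongs to Phase 1, and the sample size allows 15% loss to follow-up, which suggests that some lost participants may have no outcome.

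**Conclusion.** The point holds for Phase 1, as a minor one. The complete-case analysis estimates a shifted quantity. With non-returners resolved by tracing and viral loads missing at random among returners, it understates suppression in each arm. At planning rates with equal missingness of 5 to 20% it raises the RD by 0.3 to 1.3 points. The missing fractions are assumptions, as the article gives none. The RD bias can be zero or downward in the scenarios above, so no general claim of inflation is justified. In Phase 2 the concern applies only as far as tracing settles the status of those lost. The firmer conclusion is about purpose: complete-case analysis cannot show whether the result depends on unmeasured returners being less often suppressed. No sample-size figure is affected.

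**What to change.** Make delta-adjusted multiple imputation the sensitivity analysis for the primary outcome. Among participants in care without a viral load, lower the imputed odds of suppression step by step, separately by arm, and report the values at which the conclusion changes. Add missing counted as not suppressed as one conservative bound, described as a bound and not as an unbiased estimate. If complete-case analysis is kept, label it descriptive and state that it understates suppression in each arm when viral loads are missing at random among those in care. In Phase 2, apply the same analysis and report separately those whose status tracing could not resolve. If the SAP already contains such an analysis, only the label is needed.

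The cost is a short change of SAP wording and a few extra model runs on data already collected. The check may look less favourable than complete-case analysis would.

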### Oversight and monitoring

The University of California, Berkeley, and Health for a Prosperous Nation (HPON), a Tanzania-based non-governmental organization with expertise in HIV prevention and care that works in partnership with the Tanzanian Ministry of Health and the National AIDS Control Programme, are responsible for the study design of this trial. The co-Principal Investigators are [name] (HPON) and [name] (University of California, Berkeley) and are responsible for study supervision. Local oversight of the trial implementation is provided by HPON. This includes a dedicated study coordinator who supervises local project personnel including two regional managers (one per region) and research assistant support staff responsible for day-to-day data collection activities and monthly health facility site visits. Recruitment and enrollment targets are regularly monitored by the study coordinator, the regional managers, and the study data analyst, who is based at the University of California, Berkeley and supervised by [name]. The study coordinator and the study data analyst are responsible for facilitating biweekly team project meetings that include the study Principal Investigators and include an overview of trial conduct and progress towards study goals. Trained HBC staff are primarily responsible for identifying potential participants for Phase 1 of the study, confirming trial eligibility criteria, and for ascertaining consent for study participation. Phase 2 of the trial first consists of generation of the high-risk list, which is completed by our biostatistician team at University of California, Berkeley. This list is then shared with the HPON study staff, who work with dedicated health facility staff who are trained to use the list to recruit and enroll clients for study participation.

#### Composition of the data monitoring committee, its role and reporting structure

The study includes an independent Data and Safety Monitoring Board (DSMB) and a Data and Safety Monitoring Plan. The DSMB provides oversight of patient safety, adverse events, any study changes, and study data quality/integrity and its three voting members were chosen based on their biostatistical knowledge, expertise with the content area, and lack of conflicts of interest. DSMB meetings are held at least once per year; additional meetings are held at the discretion of the DSMB chairperson. A written report is generated by the study data analyst and shared prior to meetings with DSMB members for review. Meetings consist of an open session, where the report is reviewed, study progress is discussed, and any new conflicts of interest are declared, and a closed session, where the three voting members vote on continuation of the trial.

### Dissemination plans

Trial results will be communicated to key stakeholders through dissemination meetings and to participating health centers using language-appropriate information sheets. Investigators will present results at relevant conferences and submit manuscript(s) to peer-reviewed journals. Public access to the participant-level dataset of main trial results and statistical code will be made available via the trial registration profiles on ClinicalTrials.gov and Open Science Framework.

## Discussion

Renewed attention to the development of innovative strategies to improve lifelong retention in care among PLHIV is urgently needed to reach the ambitious UNAIDS “95–95-95” targets for ending the AIDS epidemic by 2030. In this type 1 effectiveness-implementation trial, we will evaluate an evidence-based implementation strategy—conditional economic incentives—adapted for two types of PLHIV: those out-of-care and those predicted to be at risk of disengagement using a novel, machine learning-guided approach.

In keeping with a hybrid effectiveness-implementation study design, the RKPK study aims to collect a blend of effectiveness and implementation outcomes to provide better and more actionable public health information for national decision and policymakers. Our study design considered other key elements that would promote ease of potential future scale-up of these strategies in Tanzania and beyond. First, the cluster randomized design of phase 1 of the study will allow us to understand whether there is heterogeneity of the economic incentive strategy implementation across health facilities and regions, providing key insights into how differential implementation may impact outcomes. Aside from surveys and interviews with a subset of participants, study staff have limited interaction with PLHIV in phase 1. By emulating usual care conditions, we aim to establish if strategy implementation is possible in routine settings and will help us to build the case for inclusion in the national strategy, if effective.

Phase 2 is also highly pragmatic in its utilization of routinely collected demographic, visit, and laboratory data captured in the EMR as predictors in our machine learning model. The proof of concept for this approach was shown to have 72.3% accuracy in predicting risk of disengagement among 178 PLHIV in Tanzania [58] and recently others have had similar success in correctly classifying in-care PLHIV at risk of disengaging in Ethiopia, Mozambique, and South Africa [59, 60]. Phase 2 aims to add to this small but growing body of evidence demonstrating that routine data can be effectively and accurately leveraged for use in predictive models to identify those at risk of poor clinical outcomes. We will iterate upon these successes by being the first to test whether this approach can be harnessed to proactively direct limited resources to those who may need it the most, and ultimately improve retention in care above and beyond SOC HIV services.

Our proposed study is innovative in several other ways. Economic incentives, which have been shown to be effective for an array of health outcomes including linkage and retention among ART initiates [23, 24] are a powerful yet understudied tool for improving these same outcomes among out-of-care and at-risk PLHIV. At the study’s end, we will have added to the evidence base demonstrating their use for improving lifelong retention in these two important subpopulations of PLHIV, a key research priority in sub-Saharan Africa broadly [22] and central to Tanzania’s strategy for controlling HIV specifically. In phase 2, we will build upon our experience in prior studies and implement a clinic-run mHealth system to distribute cash transfers for the improvement of patient retention in care [61]. By leveraging the widespread use of mobile money services in sub-Saharan Africa [62] with the usage of biometric (fingerprint) scanning, we provide a simple and reliable mechanism for cash transfer distribution that would be feasible to implement at scale [61]. Finally, our implementation strategy appropriately applies principles from behavioral economics and economic theory to influence care-seeking behaviors. In phase 1, we will examine a primarily behavioral economic intervention: a one-time “nudge” to return to HIV care, designed to help PLHIV to overcome present-biased preferences. In phase 2, we will have evidence demonstrating the impact of a longer incentive strategy designed to both impart habit formation as well as help to overcome structural barriers (e.g., costs) of HIV care. Together, these principles explain the potential of our approach to achieve both short- and long-term impact among out-of-care and at-risk PLHIV.

In order to reach the “95–95-95” goals by 2030, strategies that acknowledge the reality that retention in HIV care is a dynamic, lifelong process that necessitates support at different phases are needed. Findings from the intervention strategies implemented in phases 1 and 2 of this study, which incorporated key principles of implementation science, behavioral economics, and economic theory, will add critical evidence to the scant literature describing the utility of economic incentives for improving re-engagement and retention among the subpopulation of PLHIV who struggle with continuity of care. Results from our mixed methods evaluation will identify key barriers and facilitators to strategy implementation. Together, findings from the three phases of the RKPK study will inform possible adaptation and scale-up of these intervention strategies into the national strategy, which increasingly includes economic support programs and investments in machine learning and data science for health [63–65].

